monthly adherence counselling, including clinic-based pill counts and weekly reminder pill boxes which may have aided adherence. Similarly, high self-reported adherence to the study drug taken twice daily (acyclovir or matching placebo) has been observed among the HIV-infected partners within HIV-discordant couples in the trial of herpes suppression to prevent HIV transmission (“Partners in Prevention”, led by [name] in 14 African sites) with 81% having taken  $\geq 90\%$  of dispensed study drug, based on monthly pill counts and self-reported adherence data [84]. While these levels of adherence are encouraging, clinic-based pill counts are unreliable [85-89] and self-report predictably overestimates adherence by as much as 20% [90,91]. Participant reported measures may be especially problematic in highly structured clinical trial settings where there is a high level of overreporting due to social desirability bias.

In summary, results from HIV prevention trials collectively demonstrate the need for accurate and objective adherence measurement to interpret biologic efficacy. In the absence of multiple objective measures, the true level of adherence is uncertain and the extent to which adherence contributes to negative study findings is unknown. This pilot study will use two objective measures of adherence to intermittent PrEP: electronic medication monitoring using the medication event monitoring system (MEMS TrackCaps) and intracellular and plasma drug levels (see 3.3.3.2.).

MEMS TrackCap is a medication bottle cap with an embedded microchip to detect and record the date and time when the bottle is opened. Data can be uploaded wirelessly from the MEMS TrackCap to a MS-Windows based computer using a palm-sized reader. Each MEMS TrackCap has a unique serial number, can store up to 3800 events, and has a 36 month battery life. MEMS has been used successfully in ART trials in various types of resource settings. The MEMS time/date stamps create an electronic record of pill bottle–opening behaviour that is closely associated with HIV viral suppression and drug resistance [92-94].

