### 3.3.3.4 Relationship between sexual activity and adherence to HIV biomedical prevention methods.

Biologic efficacy will require that PrEP recipients have therapeutic ART drug levels at the time of sexual exposure or immediately afterwards. Studies of post-exposure prophylaxis suggest that prevention efficacy declines with the time between exposure and ART initiation [127]. Therefore, a detailed understanding of patterns of PrEP adherence and specifically how PrEP is used with respect to sexual behavior will be important to understand PrEP efficacy and guide behavioral counselling regarding optimal use.

Interactive voice response (IVR) systems have been developed to measure daily health behaviours [128-130] including alcohol use [131-133], depression [134, 135], obsessive compulsive disorder [136], smoking cessation [137, 138], gambling [139] and sexual behaviour [140]. With IVR, an automated system calls the participant's cell phone daily. The participant answers a brief set of questions by touching numbers on the telephone keypad. The lack of a human interviewer may decrease the social desirability bias inherent in person-to-person interactions, and allows for frequent data collection. IVR is currently under evaluation in Uganda to measure self-reported ART adherence [Bangsberg, unpublished]. Cell phone text messaging (SMS) has also been used successfully in an ART adherence program in the US to enhance adherence, although not to collect data [Dimagi, Charlestown MA]. The reliability and high penetration of cell phone use in Uganda makes IVR and SMS feasible.

This study will determine the relationship between sexual activity and PrEP adherence by mapping sexual behavior with daily IVR or SMS self-report and PrEP adherence with daily MEMS data. The method used, IVR or SMS, will be determined based on availability in each country. Daily assessment of sexual behavior combined with daily electronic adherence behavior is required to determine which individuals 1) sustain PrEP adherence per protocol, 2) only use preventive antiretroviral therapy according to the fixed intermittent schedule, 3) only use it just prior to sex, or 4) use it only after sex as post-exposure prophylaxis.

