#### *Study summary*

The study will allow for collection of important data on the feasibility of an intermittent/daily PrEP regimen in HIV discordant couples, and it will directly compare adherence and intracellular drug levels in daily and intermittent PrEP recipients. It will also evaluate the relationship between drug adherence, sexual behaviour and intracellular drug levels with an intermittent PrEP regimen. Specifically, this study will use timed plasma and intracellular drug levels after a witnessed dose and MEMS adherence data to model drug levels. This model can explore relationships between adherence and intracellular drug levels to determine if intracellular drug levels can be used as a surrogate adherence measure. In addition it will evaluate the relationship between adherence to an intermittent PrEP regimen and timing of sexual activity to estimate what proportion of sexual events may be 'protected' by intermittent PrEP. The pilot will use objective MEMS adherence measurement and evaluate the feasibility of newer adherence measurements such as hair sampling and plasma drug levels. The pilot will also evaluate the feasibility of using either IVR or SMS to collect sexual activity data in an African setting. It will allow study teams and communities to prepare for potential subsequent larger trials of intermittent PrEP. The pilot study is not sized to evaluate efficacy. If the pilot shows this intermittent PrEP regimen to be safe, feasible in terms of adherence, and to achieve intracellular drug levels similar to daily PrEP, this data could be used to design a larger phase 2 study with one or more intermittent PrEP regimens. The goal of such a trial would be to provide bridging data if daily PrEP regimens are found to be effective or to prepare for efficacy or non-inferiority trials of intermittent versus daily PrEP.

Investigation of immune responses associated with FTC/TDF will also be evaluated in the pilot study. The proportion of volunteers on FTC/TDF with HIV-specific immune responses will be assessed at 2-3 time points and compared to responses in volunteers assigned to placebo. Immune responses may be correlated with risk behaviour and host factors, such as HLA type. As noted above, very few HIV infections are expected to occur during the study, so correlation of HIV-specific immune responses and protection from infection or attenuation of disease progression will not be possible until a larger study is conducted.

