**Table 1**  
**Study Design**

| Investigational Product | Dosing Regimen | Route of Administration |
|-------------------------|----------------|-------------------------|
| FTC/TDF                 | Daily          | PO                      |
| FTC/TDF                 | Intermittent   | PO                      |
| Placebo                 | Daily          | PO                      |
| Placebo                 | Intermittent   | PO                      |

This study evaluates the use of FTC/TDF (FTC 200mg / TDF 300mg) or placebo;

Daily dosing: 1 tablet orally per day

Intermittent dosing: 1 tablet orally Monday and Friday and again within 2 hours after sexual intercourse (except on Monday or Friday), not to exceed 1 dose per day.

PO = Oral

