## 9.5. Behavioural Assessments

Behavioural Assessments will be assessed through IVR or SMS and follow-back interview at the time points indicated in Appendix A1.

*Interactive voice response or SMS measurement of daily sexual behavior.* Based on methods of Schroder[140], volunteers will be provided with a SIM card or a cell phone for the daily measurement of sexual behaviour using either IVR or SMS. Participants will be contacted daily to digitally answer questions similar to the following questions: 1) Did you have sex with your main partner yesterday? 2) (if yes) Did you use a condom? 3) Did you have sex with any other partner yesterday? 4) (if yes) Did you use a condom? Data will be recorded via entering the numerical response via cell phone keypad (press 1 for yes, 2 for no). Total interview time will be under 60 seconds. To encourage daily reporting, individuals will be reimbursed with 3 minutes of air time for each call. Individuals not responding will be contacted again by cell phone to elicit a response. Breach in confidentiality via unauthorized use will be prevented through automatic confirmation of the assigned cell phone number and asking the volunteer to enter a password to confirm his/her identity prior to the questions. All volunteers will have an instructive session on the use of the system.

*Follow-back interview.* The timeline follow-back interview is a calendar-aided face-to-face interviewing method during which participants are asked to retrospectively report daily sexual behaviour. This approach has shown strong retest reliability [141, 163]. Interviewers will be trained according to the method developed by Sobell and Sobell [164]. Interviewer gender will be matched to the gender of the volunteer. Volunteers will be given a customized calendar. Volunteers will be asked to mark personal “anchor” days or “holidays” on the calendar such as a market days, church attendance, national holidays, or weddings [164]. Volunteers will mark each day they had intercourse, the number of sexual partners, and code whether a condom was used. Additional risk data will be collected, such as substance use before or during sex.

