#### **14.2.4 Adherence**

The mean, median and range of adherence to PrEP will be determined using MEMS data for volunteers. Previous work has shown that the accuracy of MEMS assessment can be improved with a 3-day structured self-report of the number of extra cap openings and the number of times multiple doses are taken out of the bottle [119]. The *adjusted MEMS adherence* is calculated by the interview adjusted number of bottle openings/number of doses prescribed over the prior three days. The *unadjusted MEMS* measure is the number of electronically recorded bottle openings divided by the number of expected doses based on IVR sexual activity data, since the last interview[48]. MEMS adherence will be classified by the schema proposed by Vrijens where adherence is organized in terms of persistence and execution [161,162]. Persistence is time to treatment discontinuation. Treatment discontinuation will be defined as the first day of 30 consecutive days without a MEMS cap event. Treatment execution is defined as the number of MEMS caps events divided by the number of expected doses prior to treatment discontinuation. We also will use MEMS to characterize treatment interruptions and whether patterns of adherence are temporally related to sexual behavior. These approaches have been successfully piloted in Uganda [77,94].

For volunteers assigned to intermittent regimens, a combination of MEMS and IVR/SMS data will be used. Each day will be classified as an adherent or nonadherent day. Adherent days will be defined as: any day on which sexual activity was reported and a MEMS event occurred, any Monday or Friday on which a MEMS event occurred, and any other day of the week on which neither sexual activity nor a MEMS event occurred. Adherence will be calculated as the number of adherent days since the last visit divided by the number of days since the last visit.

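### The plan promises to separate dosing before sex from dosing after sex, but records neither the time of sex nor its order relative to the dose

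*Protocol*

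**What the plan says.** **Purpose.** Protocol Section 3.3.3.4 says daily sexual behaviour combined with daily electronic adherence data is required to sort volunteers into four patterns of use. The last two are "3) only use it just prior to sex, or 4) use it only after sex as post-exposure prophylaxis". The study summary in Section 3.7 plans to "evaluate the relationship between adherence to an intermittent PrEP regimen and timing of sexual activity" and to estimate what share of sexual events may be protected.

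**Regimen.** For the intermittent arms, Section 5.2 (Table 1) sets a tablet on Monday and Friday and "again within 2 hours after sexual intercourse (except on Monday or Friday), not to exceed 1 dose per day".

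**Measurement of dosing.** Section 3.3.3.1 says the MEMS cap can "detect and record the date and time when the bottle is opened".

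**Measurement of sex.** Section 9.5 introduces the phone items with "Participants will be contacted daily to digitally answer questions similar to the following questions". The first is "1) Did you have sex with your main partner yesterday". The other three ask about condom use and other partners, all answered yes or no. For the follow-back interview, "Volunteers will mark each day they had intercourse, the number of sexual partners, and code whether a condom was used".

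**Scoring.** In Section 14.2.4 an intermittent-regimen day is adherent if it is "any day on which sexual activity was reported and a MEMS event occurred", a Monday or Friday with an event, or any other day with neither sex nor an event. The score is adherent days divided by all days since the last visit. The same section also defines an unadjusted ratio: bottle openings divided by the doses expected from the sexual activity reports.

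**The concern.** Only one side of the comparison has a clock. The cap time-stamps the opening, but sex is placed no more precisely than a day. A volunteer who takes a tablet in the morning and has sex that evening, and one who has sex and then takes the tablet, leave the same record: sex yes, event yes. Those are the two patterns that Section 3.3.3.4 sets out to separate. Because the information is never collected, an analysis plan cannot supply it.

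The scoring rule adds to this. It uses neither the order of events nor the two-hour window, so it can credit a volunteer who never takes the post-sex dose. If days run from midnight to midnight, it can also mark down one who takes it correctly late at night. Any midnight loss arises only in the intermittent arms, while comparing adherence between the daily and intermittent regimens is a primary objective (Section 4.1).

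**Working it through.** **Figures in the plan.** The protocol gives no figure for this point. Its adherence power figures are not in dispute. An exact two-sided 0.05 binomial test of 75%, with equal tails, gives 29.2% and 66.1% at n = 24 and 50.9% and 89.6% at n = 36, against the stated 29%, 66%, 51% and 90%.

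**Step 1: can the patterns be told apart?** The records for a non-Monday/Friday day with sex in the evening are:

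| Behaviour | Phone and calendar | MEMS | Day score |
|---|---|---|---|
| Dose 08:00, sex later, none after | sex: yes | event, 08:00 | adherent |
| Sex, then dose within 2 h, before midnight | sex: yes | event, evening | adherent |

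The MEMS times differ, but with no time for the sex act neither opening can be placed before or after it. A dose on a different day from sex can still be identified. The loss is confined to same-day use.

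**Step 2: worked weeks under the adherent-day rule, reading a day as the calendar day.** Monday and Friday doses are taken in each week.

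- Sex Tuesday 23:00, dose Wednesday 00:30. Tuesday has sex and no event; Wednesday has an event and no sex. Both fail: 5/7 = 71%, although the volunteer complied fully.
- Sex Thursday 23:00, dose Friday 00:30. Only Thursday fails: 6/7 = 86%.
- Dose Tuesday 08:00, sex Tuesday 23:00, no dose after: 7/7 = 100%.

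Sex on Monday or Friday is unaffected, because no separate post-sex dose is due then.

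**Step 3: average size.** Let f be the share of correct post-sex doses that fall after midnight. The documents do not give f, so it is an assumption. Take two sex days a week among Tuesday, Wednesday, Thursday, Saturday and Sunday: ten equally likely pairs, full compliance, crossings independent. A crossing loses the sex day, unless the previous night's dose landed on that day. It also loses the next day if that day is an ordinary one without sex.

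| Pairs | Expected days lost, each |
|---|---|
| Thu–Sun | 2f |
| Tue–Thu, Tue–Sun, Wed–Sun, Thu–Sat | 3f |
| Tue–Sat, Wed–Sat | 4f |
| Wed–Thu, Sat–Sun | 2f − f² |
| Tue–Wed | 3f − f² |

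The sum is 29f − 3f², so the mean loss per week is 2.9f − 0.3f².

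- f = 25%: 0.725 − 0.019 = 0.706 days; score 1 − 0.706/7 = 89.9%.
- f = 50%: 1.450 − 0.075 = 1.375 days; score 1 − 1.375/7 = 80.4%.

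For sex days alone, the loss per sex day is f − 0.15f². Adherence on days of sexual activity is then about 76% at f = 25% and 54% at f = 50%.

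**Step 4: cross-check and the other measure.** A 16-week simulation of fully compliant volunteers used 0.25 and 0.375 sex days per day. Those rates come from the student study cited in Section 3.3.3.4, not from this population. Each cell gives the means at 0.25 / 0.375.

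| f | Day score | Sex-day adherence | Openings / expected doses |
|---|---|---|---|
| 10% | 97% / 96% | 90% / 90% | 98% / 97% |
| 20% | 95% / 93% | 81% / 81% | 96% / 95% |
| 30% | 93% / 90% | 72% / 72% | 94% / 92% |
| 50% | 88% / 83% | 54% / 56% | 91% / 88% |

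The ratio mostly still counts a late dose. It loses credit only when the opening falls on a day that already has an expected dose. A volunteer who always doses before sex and never after it scores 100% on all three measures.

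**The case against.** Several counter-arguments have force.

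- **The 80% endpoint.** A reader might infer that midnight crossings push compliant volunteers below the primary 80% threshold. The documents do not support that. The endpoint in Section 5.1.1 is 80% of expected doses, not of adherent days, and the mean openings ratio stays at 88% or more in Step 4.
- **The day boundary.** Section 14.2.4 does not say when a day starts, and Section 9.4 speaks of openings in a 24-hour period. Because time stamps are kept, another cut-off could be set at analysis. The midnight loss is therefore conditional on the calendar-day reading. A different boundary would still not reveal dose order.
- **The protected share.** A reader might infer that this cannot be estimated at all. Section 14.2.5 plans concentration curves simulated from MEMS data, and Section 3.1.4 gives intracellular half-lives of 39 hours and at least 60 hours. By simple decay, a 12-hour uncertainty shifts concentration by 1 − 2^(−12/39) = 19%, or by at most 1 − 2^(−12/60) = 13%. An approximate estimate remains possible.
- **Illustrative wording.** The phone items are only examples, so an operations manual could add a time item. Nothing in the protocol requires one, and the calendar has the same gap.
- **Not an endpoint.** Dose order appears in the rationale, not among the objectives or endpoints of Sections 4 and 5.1. That limits the weight of the point. But Section 3.3.3.4 gives this sorting as the reason for collecting daily data, and the listed items cannot deliver it.

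**Conclusion.** The point holds as a mismatch between stated purpose and instrument. As written, the protocol cannot separate same-day dosing before sex from dosing after it, and the adherent-day rule credits both. This rests on the text alone and needs no assumption about behaviour.

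The midnight effect is secondary and conditional. On a calendar-day reading, one correct late dose can take a fully compliant week to 71%. The average loss depends on the after-midnight share, which the documents do not give: mean day scores of about 90% at 25% and 80% at 50%, with two sex days a week outside Monday and Friday. It bears on the adherent-day score and on adherence during days of sexual activity (Synopsis, Statistical Considerations), and not necessarily on the endpoint of 80% of expected doses.

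**What to change.** **Data collection (Section 9.5).** After each yes to sex, add a keypad item for the time band of the act, or at least for whether a dose was taken before or after it. Add the same mark to the follow-back calendar.

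**Scoring (Section 14.2.4).** Match each act on a non-Monday/Friday day to MEMS time stamps, using the protocol's own post-sex window plus a stated tolerance for the time band. Do not count a matched event against the next day. Tabulate dose before, dose after and none.

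**Cost.** Up to two short extra items per call, since there are two partner questions, in an interview planned at under 60 seconds. Burden rises slightly and some data may go missing, both of which Section 5.1.2 already tracks as endpoints. Reported times will carry recall error, and a wide tolerance blurs the before/after split. Doses removed from the bottle in advance will still be misplaced, as Section 3.3.3.1 acknowledges for MEMS in general. No dose or clinical rule changes.

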## 9.6 Medication Sharing Assessments

Potential for medication sharing will be assessed through the follow-back interview at the time points indicated in Appendix A1.

In discordant couples, it will also be assessed by retrospective intracellular drug levels on HIV-infected partners of volunteers assigned to FTC/TDF. Blood specimens from the HIV-infected partner will be stored at 2 visits. A subset of these samples will be tested retrospectively for drug levels.

## **9.7. Other Assessments**

### **9.7.1 Drug Levels**

Plasma samples to determine drug levels and PBMC samples to determine intracellular drug levels and hair samples to determine drug levels will be collected at the time points indicated in the Schedule of Procedures (Appendix A1)

### **9.7.2 HLA Typing and other genetic analysis**

Samples for HLA typing and other genetic tests related to HIV susceptibility will be collected at the time point indicated in the Schedule of Procedures (Appendix A1).

### **9.7.3 HIV Test**

Samples will be tested at the time points indicated in the Schedule of Procedures (Appendix A1). Further information is specified in Section 11.1 HIV Testing.

### **9.7.4 Pregnancy Test**

A urine pregnancy test for all female volunteers will be performed by measurement of Human Chorionic Gonadotrophin ( $\beta$ hCG) at the time points indicated in the Schedule of Procedures (Appendix A1).

The results of the pregnancy test must be negative prior to randomization and prior to subsequent distribution of investigational product.

## **10.0 ADVERSE EVENTS**

### **10.1 Definition**

An adverse event (AE) is any untoward medical occurrence in a volunteer administered investigational product (including Placebo); it does not necessarily have a causal relationship with the investigational product. An AE can therefore be any unfavourable or unintended sign (including an abnormal laboratory finding), symptom, or disease, temporally associated with the use of the investigational product whether or not related to the investigational product.

### **10.2 Assessment of Severity of Adverse Events**

Assessment of severity of all AEs is ultimately the responsibility of the principal investigator.

The following general criteria should be used in assessing adverse events as mild, moderate, severe or potentially life-threatening:

- Mild: Mild discomfort; Minimal or no limitation of daily activities; Medical intervention not required;

- Moderate: Moderate discomfort; Some limitation of daily activities but able to work part-time or full-time with some assistance; May require minimal or no medical intervention;
- Severe: Severe discomfort; Marked limitation of daily activities, unable to work; Requires medical intervention;
- Very severe (listed as “potentially life threatening” in Appendix B): Extreme limitation in activity, significant assistance required, significant medical intervention therapy required, hospitalization required

Guidelines for assessing the severity of specific adverse events and laboratory abnormalities are listed in Appendix B, Adverse Event Severity Assessment Table.

